### Sample size and recruitment

The minimum sample size for developing a multivariable prognostic model to predict recovery for patients with idiopathic SSNHL was estimated using the method reported by Riley *et al*.^14^ Assuming a prevalence (ie, full recovery of idiopathic SSNHL) of between 32% and 65%,^2 8 9^ a Nagelkerke’s R-squared of 0.5,^14^ a 0.05 margin of error in estimation of intercept, and a shrinkage factor of ≥0.95, with our prespecified number of predictor parameters of 15, resulted in a minimum sample size of 510 patients. Assuming that 70% of patients with SSNHL are idiopathic cases, this gives a total study minimal sample size of 730 patients.^3 4^

Ninety-seven NHS trusts across the UK have been identified as study sites via INTEGRATE, SFO-UK, NIHR CRN Audiology Champions and the NIHR CRN. An audit carried out in preparation of this study at five NHS trusts, over 6 months, revealed an average presentation rate of one patient with idiopathic SSNHL per trust per month. It appears therefore that our recruitment target over the study duration (32 months) is feasible.

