### Candidate predictors for prognostic model

Age; gender; social class; presence of vestibular symptoms; precipitating illness; pattern of hearing loss; severity of hearing loss; time between onset of symptoms and treatment; treatment(s) received.

Pattern of hearing loss will be defined as: low frequency loss (250 Hz, 500 Hz and 1000 Hz), mid-frequency loss (500 Hz, 1000 Hz and 2000 Hz), high-frequency loss (2000 Hz, 4000 Hz and 8000 Hz) and all frequencies. Severity of hearing loss (on presentation) will be defined as follows: pure tone average (PTA) across six frequencies (250 Hz, 500 Hz, 1000 Hz, 2000 Hz, 4000 Hz and 8000 Hz), classified as: mild (25–40 dB loss), moderate (41–70 dB loss), severe (71–95 dB loss) and profound (>95 dB loss).

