### Statistical analysis

We will develop a prognostic model to predict recovery for patients with idiopathic SSNHL and assess the impact of idiopathic SSNHL on patients’ QoL. A multivariable prognostic model will be developed using the candidate predictors specified above (n=15). Missing outcome data at the end of the study will be imputed using multiple imputation by a chained equations procedure.^15^ Internal validation will be performed to quantify optimism in the predictive performance (calibration and discrimination) of the developed model using bootstrapping techniques. Bootstrapping techniques provide information on the performance of the model in comparable datasets and generate a shrinkage factor to adjust the regression coefficients.^16 17^

The mean change in HHIA, HHIE and HUI3 scores across patients with idiopathic SSNHL will be calculated from initial presentation to follow-up (any one time between 6 and 16 weeks). We will use the non-parametric Wilcoxon and McNemar–Bowker tests with a significance level of 5%. Statistical analysis will be carried out using R V.3.6.2 (R Foundation for Statistical Computing, Vienna, Austria).

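### Presentation hearing loss enters the prognostic model as four bands of a continuous dB average, which discards part of its predictive information; it should enter as a continuous term.

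*Protocol article*

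**What the plan says.** The section Candidate predictors for prognostic model lists nine predictors, among them "pattern of hearing loss; severity of hearing loss; time between onset of symptoms and treatment; treatment(s) received". It defines severity at presentation as a "pure tone average (PTA) across six frequencies (250 Hz, 500 Hz, 1000 Hz, 2000 Hz, 4000 Hz and 8000 Hz"), then "classified as: mild (25–40 dB loss), moderate (41–70 dB loss), severe (71–95 dB loss) and profound (>95 dB loss").

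The Statistical analysis section states: "A multivariable prognostic model will be developed using the candidate predictors specified above (n=15"). Nothing in the article keeps PTA continuous for the model, mentions a spline or other flexible term, or gives a reason for the bands.

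The section Sample size and recruitment gives the size of the model: "with our prespecified number of predictor parameters of 15, resulted in a minimum sample size of 510 patients". It does not allocate the 15 parameters to the nine predictors.

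Under Secondary outcomes, thresholds beyond the limit of the audiometer are scored as 96 dB at that frequency.

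**The concern.** Predicting recovery is the second of the three study objectives and the one that sets the sample size. The Introduction names degree of hearing loss among the factors on which prognosis may depend. The plan measures that factor on a dB scale and then reduces it to four steps before fitting.

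The moderate band, 41-70 dB, spans about 30 dB, three times the 10 dB margin that defines full recovery under Primary outcome. Within a band the model cannot separate ears by severity. At a band limit it imposes a jump that a 1 dB difference does not justify. The plan will assess both calibration and discrimination, and both are affected. Bootstrapping and shrinkage correct optimism; they cannot restore information removed before the model is fitted.

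This is not a detail left to an unseen analysis plan. The protocol states the coding, and a later document that used continuous PTA would depart from it.

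**Working it through.** **1. The plan's own figure.** Inputs from Sample size and recruitment: full recovery 32% to 65%, Nagelkerke "R-squared of 0.5", "a 0.05 margin of error in estimation of intercept", shrinkage at least 0.95, 15 parameters. With max R²(CS) = 1 − exp{2[p ln p + (1−p) ln(1−p)]} and R²(CS) = 0.5 × max, the shrinkage criterion is n = P / {(S−1) ln(1 − R²(CS)/S)}. For P = 15 and S = 0.95 it gives 636 (p = 0.32), 598 (p = 0.50) and 624 (p = 0.65). The intercept criterion, (1.96/0.05)² p(1−p), gives 335 to 385. The stated 510 is therefore not reproduced; 510/0.70 = 729 does agree with the stated 730. That mismatch is a separate matter. Below, 510 is taken as the plan's model sample size.

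**2. Variance kept by the bands.** The protocol gives no PTA distribution, so several are assumed. For a uniform distribution of range R cut into bands of width w, the share of variance lost is Σw³/R³. Cuts are at 40.5, 70.5 and 95.5 dB.

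| Assumed PTA | Widths (dB) | Σw³/R³ | Lost |
|---|---|---|---|
| Uniform 30-110 | 10.5, 30, 25, 14.5 | 46,831/512,000 | 9.1% |
| Uniform 25-100 | 15.5, 30, 25, 4.5 | 46,440/421,875 | 11.0% |
| Uniform 25-96 | 15.5, 30, 25, 0.5 | 46,349/357,911 | 13.0% |
| Normal (65, 25) limited to 25-115 | numerical | 1 − 0.875 | 12.5% |

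A second measure, the likelihood-ratio information in severity, was simulated with odds ratios of 0.6-0.8 per 10 dB. The distributions were uniform 25-110, uniform 25-96 and normal (65, 22) limited to 25-110. The loss was about 8-16%.

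**3. What a band does to individual risks.** Assume an odds ratio of 0.7 per 10 dB, normal (65, 22) PTA limited to 25-110 dB, and severity alone in the model.
- At 32% recovery, true risk is 0.51 at 41 dB and 0.27 at 70 dB; the moderate band gives both 0.38.
- At 65% recovery, the values are 0.83 and 0.63; the band gives both 0.72.
- At 50% recovery, true risk at 70 dB is 0.46. The odds at 71 dB are 0.46/0.54 × 0.7^0.1 = 0.82, a risk of about 0.45. The bands give 0.57 at 70 dB and 0.37 at 71 dB.

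**4. Effect in a model of the planned size.** Simulation: n = 510, 200 replicates, each evaluated on 5,000 new patients. The linear-predictor SD is 2.04, chosen to give Nagelkerke R² of about 0.5. PTA is uniform over 30-110 dB with a linear logit effect. One other predictor carries the remaining signal and 11 covariates carry none. The banded model has 3 + 1 + 11 = 15 parameters and the three-knot spline model 2 + 1 + 11 = 14.

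| Severity's share of signal | RMSE of risk, bands | RMSE of risk, spline |
|---|---|---|
| 10% | 0.084-0.087 | 0.075-0.076 |
| 25% | 0.094 | 0.075 |
| 50% | 0.108-0.109 | 0.074-0.075 |

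Where two values are shown, separate runs differed slightly. The c-statistic is lower with bands by 0.003 to 0.011.

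**5. Sensitivity to the PTA range.** In a smaller model with only one other predictor, moving from 30-110 to 25-96 dB widened the RMSE gap between bands and spline. At a 25% share it went from 0.068 − 0.034 = 0.034 to 0.082 − 0.034 = 0.048. At a 50% share it went from 0.086 − 0.034 = 0.052 to 0.110 − 0.034 = 0.076. Only the direction carries over to the full-size model.

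**The case against.** The case on the other side has several parts.

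- **The loss is modest.** A c-statistic difference of at most about 0.011 is small, and the shares of 10-50% have no source in the protocol. This stands, and it limits the size of the claim. The error in predicted risk is the more telling measure.
- **Error more than doubled.** A reader might infer this from a model with severity and one other predictor compared with a straight-line term. The plan fits 15 parameters, whose estimation error is common to both codings. Against the spline proposed here the ratio is 0.084/0.075 = 1.1 to 0.109/0.075 = 1.5.
- **A large loss of power.** A reader might infer this by comparing a test of a single linear term with a test of three band terms. The protocol plans a prediction model and no test of severity, and the spline would itself spend a second degree of freedom.
- **Three wasted parameters.** The protocol does not allocate its 15. Three for severity assumes nominal coding, and the spline uses two, so the saving is at most one.
- **Biased treatment comparisons.** A reader might infer that banding weakens adjustment when effects of treatment or delay are read from the model. The stated objective is prediction; no such reading is planned.
- **The 96 dB code.** A no-response frequency can score better than a measured threshold above 96 dB, so continuous PTA is distorted at the top, where the open band pools such ears. This stands and the fix must deal with it. It does not justify banding 25-95 dB.
- **Absolute PTA is not the gain needed.** Recovery is judged against a reference that differs between patients, so neither coding measures distance to recovery. This stands; continuous coding cures the banding loss only.

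**Conclusion.** The protocol fixes a banded model input where the dB value is available, and this loses information. The loss is about 9-13% of the PTA variance under the four distributions in the table. In a 15-parameter model with 510 patients, the RMSE of predicted risk is about 0.084-0.109 against about 0.075 with a three-knot spline, and the c-statistic is about 0.003-0.011 lower. The gap is larger if PTA spans 25-96 dB.

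These sizes rest on assumed PTA distributions, an effect linear on the logit scale and an assumed share of signal, because the protocol gives none of them. The direction is clear and the size moderate. The model can still be developed with the bands, but with avoidable error in individual predictions. Getting the same severity contribution does not mean getting the same predicted risk: pattern of loss and the other predictors still separate ears within a band.

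**What to change.** - In Candidate predictors for prognostic model, state that presentation PTA enters the model in dB as a restricted cubic spline with three knots (2 parameters). Keep the four bands for descriptive tables only.
- Because out-of-limit thresholds are coded 96 dB, either apply one consistent cap at the top of the scale or add an indicator for out-of-limit ears, so that no response does not score better than a measured threshold above 96 dB.
- Restate the parameter count in Sample size and recruitment and in Statistical analysis if it changes. The spline saves at most one parameter, assuming nominal coding of the bands; an out-of-limit indicator would use that one.

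The cost is a few sentences of analysis wording. Audiometry results are already collected at both visits, so no new data are needed. The one drawback is that the model will need a formula or calculator instead of a lookup table.

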### Primary outcome

The change in auditory function in the affected ear from initial presentation to follow-up (at any one time between 6 and 16 weeks from onset of symptoms). Auditory function will be defined as the PTA of air conduction thresholds between the following specific frequencies: 250 Hz, 500 Hz, 1000 Hz, 2000 Hz, 4000 Hz and 8000 Hz. If multiple pure tone audiograms have been carried out between 6 and 16 weeks, the most recent pure tone audiogram will be used for the calculation of auditory function.

Change in auditory function classified as:

Full recoveryFinal PTA in affected ear within 10 dB (≤10 dB) of PTA of baseline pure tone audiogram.OR should a baseline pure tone audiogram not be available:Final PTA in affected ear within 10 dB of PTA of unaffected ear.OR should both ears be affected with hearing loss:Final PTA in affected ear within 10 dB of a normative reference (ISO7029).

Partial to no recoveryFinal PTA in affected ear ≥10 dB of PTA of baseline pure tone audiogram.OR should a baseline pure tone audiogram not be available:Final PTA in affected ear ≥10 dB of PTA of unaffected ear.OR should both ears be affected with hearing loss:Final PTA in affected ear ≥10 dB of PTA of a normative reference (ISO7029).^13^

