**Trial registration number:**

ClinicalTrials.gov Registry (NCT04108598).

Strengths and limitations of this studyTaking place across 97 National Health Service trusts, the SeaSHeL Study represents the first nationwide prospective cohort study of adults presenting to ear, nose and throat (ENT) and hearing services with sudden sensorineural hearing loss (SSNHL).It is uniquely delivered by National ENT Trainee Research Network, Student and Foundation Doctors in Otolaryngology, National Institute for Health Research (NIHR) Clinical Research Network (CRN) Audiology Champions and the NIHR CRN.We acknowledge that duration between onset of SSNHL and presentation to ENT services as well as follow-up times and treatment strategies will vary across centres and cases, which may impact measured outcomes; however identifying differences in the patient pathway will form an important study finding.

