### Study procedures

A summary of study procedures is outlined in figure 1. Box 1 provides a summary of all data to be collected. Adult patients with SSNHL presenting to any of the 97 NHS trusts will be assessed for eligibility. In 20 of 97 NHS trusts, all data identified in box 1 will be collected. In the remaining 77 trusts, all data except for QoL data will be collected. In centres where no QoL data are collected, there will be no deviation from the usual standard of care for any patient, and routinely collected patient data will be anonymised; therefore, consent is not required. For centres where QoL data are collected, patients will be provided with a study information sheet and requested to give written consent to participate in the study.

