**Figure 1 F1:**
[figure not shown]
Summary of study procedures. A brief outline of study procedures from patient recruitment to data analysis. QoL, quality of life; SSNHL, sudden sensorineural hearing loss.

Box 1Data to be collectedGeneral information.Patient demographics and socioeconomic status.Medical history and social history.Patient’s first presentation to ear, nose and throat (ENT).Hospital and service patient presenting to.Date of presentation.Referral pathway and treatments received up until first presentation to ENT.Clinical history of sudden sensorineural hearing loss (SSNHL).Examination findings.Audiometry results.Imaging requests/results.Laboratory test requests/results (data on any laboratory test requested for a patient with SSNHL to be collected).Vestibular function tests/results (data on any vestibular function test requested for a patient with SSNHL to be collected).Hearing Handicap Inventory for Adults (HHIA) Questionnaire score OR Hearing Handicap Inventory for Elderly (HHIE) Questionnaire score.*Health Utility Index Mark 3 (HUI3) Questionnaire score.*Treatment plan.Cause of SSNHL identified.Follow-up details.Follow-up (6–16 weeks after onset of symptoms).Date of presentation.Examination findings.Audiometry results.Imaging requests/results.Laboratory test results (data on any laboratory test requested for a patient with SSNHL to be collected).Vestibular function results (data on any vestibular function test requested for a patient with SSNHL to be collected).HHIA Questionnaire score OR HHIE Questionnaire score.*HUI3 Questionnaire score.*Treatments provided since first visit to ENT.Cause of SSNHL identified.Adverse events.*To be collected at quality of life sites only (20 of 97 sites).

Patient follow-up data will be collected at 6–16 weeks from onset of symptoms. All data collected will be uploaded onto REDCap, a secure online data collection platform.^18 19^ All data will be transferred and stored in accordance with data governance regulations (Data Protection Act 2018).

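### At the 77 usual-care trusts the outcome exists only if a routine audiogram falls at 6-16 weeks, so missingness may depend on recovery, and no earlier audiogram is listed to correct it

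*Protocol article*

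**What the plan says.** All references are to the protocol article.

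- **Primary outcome.** Change in auditory function is measured "from initial presentation to follow-up (at any one time between 6 and 16 weeks from onset of symptoms". There is a rule for several audiograms inside the window: "If multiple pure tone audiograms have been carried out between 6 and 16 weeks, the most recent pure tone audiogram will be used". There is none for a patient whose last audiogram precedes week 6.
- **Study procedures.** At centres without quality-of-life collection (77 trusts), "there will be no deviation from the usual standard of care for any patient", and the data are those gathered routinely. For the other trusts the article says "In 20 of 97 NHS trusts, all data identified in box 1 will be collected". It does not say whether those 20 add a visit.
- **Box 1 and the text after it.** Audiometry is listed at first presentation and again at follow-up. The timing is repeated: "Patient follow-up data will be collected at 6–16 weeks from onset of symptoms".
- **Statistical analysis.** "Missing outcome data at the end of the study will be imputed using multiple imputation by a chained equations procedure". The variables in the imputation model are not given.
- **Strengths and limitations.** The article accepts that "follow-up times and treatment strategies will vary across centres and cases, which may impact measured outcomes".
- **Introduction.** Care pathways, follow-up included, are described as differing considerably. Spontaneous recovery is put at 32%-65%, with a caution that this may be too high.

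**The concern.** At 77 trusts no study procedure secures the audiogram that defines the outcome. Whether it exists depends on local practice and on whether the patient comes back, and a patient whose hearing has returned may have less reason to do so. If hearing is recorded as recovered at, say, week 4 and not tested again, the clinical record holds direct evidence of the outcome, yet the data set as listed codes that outcome as missing.

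Chained-equations imputation in its usual form assumes that, given the collected variables, missingness does not depend on the unseen outcome. The variable that would make this plausible here is the last audiogram before the window, and it is not among the listed data.

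Two products are at stake. One is the recovery proportion, which is among the outcome data meant to inform a later trial. The other is the calibration of the prognostic model. Bootstrap validation would not expose the error, because every resample carries the same missingness.

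**Working it through.** The article gives no rate of missing outcomes and no rate of discharge before week 6, so there is no figure of the plan's own to reproduce. The missing shares below are assumptions.

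**Inputs.** True recovery p: the sample-size section works from "Assuming a prevalence (ie, full recovery of idiopathic SSNHL) of between 32% and 65" per cent; the midpoint is (0.32 + 0.65)/2 = 0.485. Missing share among recovered patients: mR. Missing share among unrecovered patients: mU. Nagelkerke R-squared: 0.5, from the sample-size section.

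**Step 1: complete cases.** Observed recovery = p(1 - mR) / [p(1 - mR) + (1 - p)(1 - mU)].

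For p = 0.485, mR = 0.20, mU = 0.10: 0.388 / (0.388 + 0.4635) = 0.456.
For p = 0.485, mR = 0.30, mU = 0.10: 0.3395 / (0.3395 + 0.4635) = 0.423.

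| mR | mU | p = 0.32 | p = 0.485 | p = 0.65 |
|---|---|---|---|---|
| 0.10 | 0.10 | 0.320 | 0.485 | 0.650 |
| 0.20 | 0.10 | 0.295 | 0.456 | 0.623 |
| 0.30 | 0.10 | 0.268 | 0.423 | 0.591 |
| 0.10 | 0.20 | 0.346 | 0.514 | 0.676 |
| 0.10 | 0.30 | 0.377 | 0.548 | 0.705 |

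Equal missingness gives no bias. The sign follows whichever group is missing more often.

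**Step 2: after imputation from baseline.** The plan imputes, so the complete-case figures are not what it would report. A simulation of 200,000 patients used one baseline predictor with a logistic coefficient of 2.05, giving Nagelkerke R-squared of about 0.5. The outcome model was fitted to patients with an observed outcome, and missing outcomes were replaced by their fitted probabilities.

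| mR | mU | True | Complete cases | After imputation | Remaining bias |
|---|---|---|---|---|---|
| 0.20 | 0.10 | 0.485 | 0.456 | 0.468 | -0.017 |
| 0.30 | 0.10 | 0.483 | 0.422 | 0.447 | -0.036 |
| 0.20 | 0.10 | 0.326 | 0.301 | 0.311 | -0.015 |
| 0.30 | 0.10 | 0.328 | 0.275 | 0.295 | -0.033 |
| 0.20 | 0.10 | 0.645 | 0.618 | 0.629 | -0.016 |
| 0.30 | 0.10 | 0.646 | 0.586 | 0.610 | -0.036 |

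Imputation removes part of the bias and leaves about 2 to 4 points.

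**Step 3: model coefficients.** If missingness depends on recovery alone, the intercept shifts by ln[(1 - mR)/(1 - mU)]: ln(0.80/0.90) = -0.12 and ln(0.70/0.90) = -0.25. In the simulation at p near 0.485 the intercept moved from -0.100 to -0.217 and from -0.108 to -0.355, in line with this. The slope stayed put (2.053 to 2.049; 2.050 to 2.051). Slopes are distorted only if, among patients with the same recovery status, missingness also varies with the predictor.

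**The case against.** The strongest reply is that the mechanism is assumed. Nothing in the article says that recovered patients leave before week 6 or when recovery happens, and unrecovered patients might equally drop out or seek care elsewhere. This stands. A reader might infer that the plan will understate recovery; the documents do not settle the sign, the size, or whether there is any bias.

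Second, imputation is planned. A reader might set the complete-case error of up to 6 points against the 0.05 margin in the sample-size section and call it a breach. That does not hold. After imputation the remaining error in these scenarios is 2 to 4 points, and 0.05 is a sampling-precision input, not a tolerance for bias.

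Third, the statement that usual care is unchanged covers only the trusts without quality-of-life collection. It does not support a claim that no trust adds a visit.

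Fourth, Box 1 is a summary in a condensed article, it includes an item for follow-up details, and imputation variables and sensitivity analyses are usually left to the SAP. This stands in part: fuller case report forms might already capture interim audiograms. But the article presents Box 1 as covering all the data, and an SAP cannot use audiograms that were never captured.

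Last, a fixed window from onset gives a comparable horizon, ten weeks is wide, and the limitations section mentions variable follow-up. The window itself is defensible. The acknowledged limitation, however, concerns timing and treatment differences; it does not address an outcome that is absent because of recovery, and it offers no remedy.

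**Conclusion.** The point holds as a risk. At 77 of 97 trusts, the window combined with usual-care follow-up and no listed interim audiometry means that observation of the outcome may depend on recovery itself, and imputation from baseline variables alone cannot fully correct that.

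Under the assumed 20-30% against 10% missing, a recovery proportion near 0.485 would be reported about 2 to 4 points low after imputation (3 to 6 points in complete cases), with an intercept shift of -0.12 to -0.25. Reversed shares would push it up, and equal shares would leave it unbiased. The simulation rests on a single baseline predictor with R-squared of about 0.5; weaker predictors would recover less.

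The effect falls mainly on the recovery proportion, the intercept and calibration. A reader might also infer biased predictor effects, but that needs missingness to depend on the predictor given recovery, for which the article offers no evidence. The change is worth making because it is cheap and the data cannot be supplied by analysis later.

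**What to change.** 1. Add to the Box 1 data the date and thresholds of the last routine audiogram before week 6 and, where already on record, of the first after week 16.
2. Use these as auxiliary variables in the imputation model for the primary outcome.
3. Prespecify a sensitivity analysis that classes a patient with documented full recovery before week 6 and no later audiogram as fully recovered.

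The primary outcome window stays as it is, and no visit or test is added. The cost is a few more fields taken from existing records and one further analysis. The downside is the added data entry and that the sensitivity analysis assumes early recovery lasts, which should be said when it is reported.
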